### Ultrasound measurements

The blinded primary investigator will perform cyst diameter measurements by ultrasonography. The treated hepatic cyst will be visualized in two planes to measure each maximal orthogonal diameter (craniocaudal, anteroposterior and mediolateral) three times. As a secondary endpoint, cyst volume will be estimated by multiplying the maximum of each orthogonal diameter by 0.523 [10]. The measurement will be performed using a 3.5 MHz convex transducer (Acuson X150™, Siemens Healthcare, Erlangen, Germany). A blinded independent investigator will repeat all measurements. Both investigators are trained and experienced in measuring hepatic cyst diameter.

### Patient-reported outcome measures

Abdominal symptoms and health-related quality of life will be assessed at screening and during follow-up visits. The standardized gastrointestinal symptom questionnaire (GIS) assesses 11 abdominal symptoms using a seven-point Likert scale ranging from 0 (‘none’) to six (‘severe’) [21]. The Medical Outcomes Study 36-item short-form health survey (SF-36) will be completed to evaluate health-related quality of life [22]. This generic questionnaire assesses health-related quality of life in eight different domain scores and two summarizing (physical and mental) component scores. Additionally, a disease-specific questionnaire for PLD in development (PLD-Q, Radboud University Medical Center, Nijmegen) that assesses frequency and discomfort of 16 PLD-related symptoms over a timeframe of one month, will be completed by all subjects in order to validate this instrument in patients treated for large symptomatic hepatic cysts.

### Study procedures

This study consists of seven visits including one screening visit, three treatment visits and three follow-up visits.

#### Screening visit (within four weeks prior to starting the trial)

Potential subjects with an indication for AS will be asked to participate. Informed consent will be obtained from all participants. Upon providing informed consent, each subject will be screened for eligibility during a separate screening visit performed within 28 days prior to the start of the trial. During this screening visit the following assessments will be made:obtain written informed consent;extensive medical history and physical examination;laboratory markers: potassium, calcium, magnesium, estimated glomerular filtration rate calculated by the Modification of Diet in Renal Diseases (MDRD) formula, platelets, INR, alanine aminotransferase (ALT), aspartate aminotransferase (AST), alkaline phosphatase (ALP), gamma-glutamyl transpeptidase (GGT), total bilirubin (TB), albumin and fasting blood sugar (FBS);urine pregnancy test in female patients with childbearing potential;electrocardiogram: frequency, QTc and atrioventricular conduction;ultrasonography: cyst diameter and volume measurement andquestionnaires: GIS-, PLD- and SF-36 questionnaire.

#### First injection (week 0)

The first injection will be administered 14 days prior to AS and indicates the start of this trial. Patients in the treatment arm will receive the first injection of pasireotide LAR 60 mg, while patients in the placebo arm will receive an injection of the sodium chloride solution. The injections will be administered by an independent unblinded health professional who is not involved in the design, execution or analysis of the trial.

#### Aspiration sclerotherapy (week two)

Patients will be admitted the day of AS. Prior to the intervention, adverse events in the previous two weeks will be assessed. Moreover, blood will be drawn to evaluate safety laboratory markers (potassium, magnesium, FBS, ALT, AST, TB and amylase). AS will be performed following standard procedure in both arms. Aspirated cyst fluid will be stored in our laboratory for future analyses.

#### Second injection (week four)

Two weeks following AS (four weeks following the first injection) the patient will visit the outpatient clinic to receive the second injection. Cyst diameter will be assessed. All adverse events will be documented and blood will be obtained. If the following laboratory parameter levels are found, the second injection will not be administered:FBS >9.9 mmol/l;AST or ALT >5 × upper limit of normal (ULN);AST or ALT >3 × ULN with TB >2 × ULN oramylase >10 × ULN.

If the parameters fall within the margin of safety, the second injection will be administered.

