#### Exclusion criteria

The aspiration sclerotherapy-related exclusion criteria are as follows:Suspicion of a complicated hepatic cyst (active cyst hemorrhage, rupture, or infection),Coagulopathy (international normalized ratio (INR) >2 or platelet count <80 × 10^9^/l) orSevere co-morbidity contraindicating anesthesia (ASA 4 classification).

The pasireotide treatment-related exclusion criteria are as follows:Known long QT syndrome and/or corrected QT interval (QTc) at screening >470 ms;Family history of long QT syndrome or idiopathic sudden death;Uncontrolled or significant cardiac disease including a recent myocardial infarction, congestive heart failure, unstable angina or sustained and/or clinically significant cardiac arrhythmias;Risk factors for torsades de pointes: hypokalemia, hypomagnesemia, hypocalcaemia, clinically significant bradycardia or high grade atrioventricular block;Concomitant disease that could prolong QT interval such as autonomic neuropathy, HIV, cirrhosis, uncontrolled hypothyroidism or cardiac failure;Use of anti-arrhythmic medicinal products or other substances known to lead to QT interval prolongation;Symptomatic cholecystolithiasis;Uncontrolled diabetes, defined as glycated hemoglobin (HbA1C) level >64 mmol/ml despite adequate therapy;Moderate to severe hepatic impairment defined by a Child-Pugh classification of more than six points;History of acute pancreatitis;Hypersensitivity to somatostatin analogues or any component of pasireotide orNon-malignant medical illnesses that are uncontrolled or whose control may be jeopardized by the treatment with the study therapy.

Further exclusion criteria are as follows:Pregnant or nursing women,Use of oral contraception or estrogen supplementation,Intervention (aspiration with or without sclerotherapy or surgical intervention) within six months prior to baseline,Treatment with somatostatin analogues within six months prior to baseline orAny current or prior medical condition that may interfere with the conduct of the study or the evaluation of its results in the opinion of the investigator.

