#### Pasireotide

Subjects in the active treatment arm will receive two intragluteal injections of 60 mg pasireotide (SOM230, Novartis, Basel, Switzerland) long-acting release (LAR). The first injection will be administered two weeks prior to AS, the second injection will be administered two weeks following AS. Pasireotide LAR, powder for suspension for injection, is a one-month depot microparticle formulation for intramuscular administration. No dose adjustment is required for race, age, gender, body weight, mild hepatic impairment or renal impairment. The most common adverse events are gastrointestinal by nature and include mild diarrhea, nausea and abdominal pain [18]. These events are more frequent in the first days after treatment initiation and mitigate within time. Moreover, transient hyperglycemia, local injection site skin reactions and headaches are common side effects of pasireotide [18,19]. Previous studies have indicated that pasireotide may prolong the QT interval [20]. Therefore, patients with a prolonged QTc at screening (>470 ms) are not eligible to participate in this study. Known long-term side effects, such as development of gallstones, are not expected in this study given the limited number of injections.

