### Study withdrawal

Subjects can withdraw informed consent and leave the study at any time. The investigator will withdraw a subject from the study for any of the following reasons: pregnancy, consistent failure to adhere to protocol requirements, unacceptable toxicity of study medication, surgical interventions during the study or any other reason if in the best interest of the patient. All data generated up to the time of discontinuation from the study will be analyzed and the reason(s) for discontinuation will be recorded.

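### The rule for the second injection has no condition for low potassium, magnesium or calcium, although each of these bars entry as a torsades risk factor

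*Protocol article*

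**What the plan says.** The section on the second injection (week four) of the protocol article introduces its limits with "If the following laboratory parameter levels are found, the second injection will not be administered". Four conditions follow:

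- FBS above 9.9 mmol/l
- AST or ALT above 5 times the upper limit of normal (ULN)
- AST or ALT above 3 times ULN together with total bilirubin (TB) above 2 times ULN
- amylase above 10 times ULN

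The section closes with "If the parameters fall within the margin of safety, the second injection will be administered". It says that blood is taken at this visit but does not name the panel.

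Three other sections bear on this rule. The exclusion criteria bar patients with "Risk factors for torsades de pointes: hypokalemia, hypomagnesemia, hypocalcaemia, clinically significant bradycardia or high grade atrioventricular block". The description of the drug says "Previous studies have indicated that pasireotide may prolong the QT interval" and calls the product a "one-month depot microparticle formulation for intramuscular administration". At the sclerotherapy visit two weeks earlier, "blood will be drawn to evaluate safety laboratory markers (potassium, magnesium, FBS, ALT, AST, TB and amylase"; no action is attached to the results.

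**The concern.** The article treats low potassium, magnesium and calcium as serious enough to keep a patient from a first dose, because the drug may act on the QT interval. At the second dose the same states have no place in the rule. The other safety markers drawn at week two all reappear there; the two electrolytes do not.

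What is at stake is patient safety at one decision. A depot injection cannot be taken back once given, so the check has to come before it. With no stated limit, a low electrolyte at week four is left to the judgment of whoever sees the result, while glucose, liver enzymes and amylase have fixed limits.

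**Working it through.** The plan has no figure to reproduce here, so the check sets the sections side by side.

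**Which analytes are measured, and which are acted on**

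| Analyte | Screening panel | Week-two panel | Condition at second injection |
|---|---|---|---|
| Potassium | yes | yes | none |
| Magnesium | yes | yes | none |
| Calcium | yes | no | none |
| FBS | yes | yes | above 9.9 mmol/l |
| ALT, AST | yes | yes | above 5 × ULN, or above 3 × ULN with raised TB |
| TB | yes | yes | only jointly with AST/ALT |
| Amylase | no | yes | above 10 × ULN |

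The week-two panel has 7 markers. Of these, 4 (FBS, ALT, AST, amylase) have a limit of their own at week four, 1 (TB) has a joint limit, and 2 (potassium, magnesium) have none: 4 + 1 + 2 = 7. Of the 3 electrolytes in the torsades exclusion, 0 appear in the 4 withholding conditions. Calcium is not named in any panel after screening.

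**Whether another listed check fills the gap**

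- An electrocardiogram is listed at screening and at no later visit.
- The follow-up panel at weeks 6, 14 and 26 is FBS, ALT, AST, ALP and GGT, with no electrolytes.
- The last named potassium and magnesium results therefore come from week two (day 14), which is 28 − 14 = 14 days before the second injection on day 28.

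**Timing**

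The Discussion puts peak drug levels about 20 days after a depot injection. For the second injection that is about day 28 + 20 = 48. The primary ultrasound is at week six, day 42, so 42 − 28 = 14 days after the second injection. Week four is the last point at which exposure from that injection can be prevented.

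**Size**

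The drug risk falls on the pasireotide arm, at most 17 patients. The article gives no rate of low potassium, magnesium or calcium, so an expected number affected cannot be calculated.

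**The case against.** The strongest reply is that this is a journal article, which may leave electrolyte handling to the full protocol. The week-four visit is visibly condensed, since its blood panel is not even named. An entry criterion need not be repeated before each dose, and the article does not list low potassium or magnesium among the drug's side effects. A low value found at week two could be corrected in the following fortnight, and nothing forbids that. There is also an independent safety board.

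Part of this stands. It keeps the point minor, and the full protocol may already hold the missing line. It does not remove the point, because the article is not silent: it gives a list of limits and then an instruction to dose. The word for parameters in that instruction could be read to cover all safety bloods, but no electrolyte limit is given on that reading either.

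A reader might infer two stronger things.

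- **That a patient with a low electrolyte will be re-dosed.** The documents do not show this. The withdrawal section says "The investigator will withdraw a subject from the study for any of the following reasons" and ends its list with "any other reason if in the best interest of the patient", so a clinician can step in. That clause concerns leaving the study, on judgment and without a threshold, so it is no substitute for a dosing rule.
- **That the only alternative to dosing is withdrawal, with loss of the week-six ultrasound.** This is not supported. The dosing rule itself withholds the injection for other laboratory values without calling for withdrawal. The analysis section puts anyone with at least one dose in the ITT set and reserves the per-protocol set for those with both injections. A missed second dose is thus provided for.

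**Conclusion.** The point holds as a minor patient-safety gap. Read literally, the second-injection rule permits a further depot dose in a patient whose potassium, magnesium or calcium would have barred entry, and no other listed check at or before that visit sets a limit. It is a gap in a stated rule. It does not make the sections contradict each other, and it is not evidence that patients will be harmed.

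The exposure is small: at most 17 patients on active drug, two injections each, after extensive QT-related exclusions. The power and type I error claims are unaffected. The conclusion assumes that the list of limits in the article is the rule in force. If the full protocol already has electrolyte limits, only the article's wording is incomplete.

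**What to change.** Name potassium, magnesium and calcium in the week-four blood. Add to the rule, for both arms, that the second injection is not given while any of the three is below the limit used for the entry exclusion. The value is corrected first, and the injection is omitted if correction is not achieved within a short window that the sponsor sets. State that the patient then stays in the study and in the ITT set, and that all ultrasound visits keep their original dates.

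The window should be short because a delay of d days leaves 14 − d days between the second injection and the primary ultrasound.

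The cost is small:

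- At most 3 × 34 = 102 extra laboratory results on blood already drawn, fewer if the full panel already contains some of them.
- An occasional delayed or omitted injection. A delayed injection still counts as received. An omitted one removes the patient from the per-protocol set, where the sample size leaves 34 − 30 = 4 patients for violators and dropouts.

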#### Follow-up visits (week six, 14 and 26)

Three follow-up visits will be planned at six, 14 and 26 weeks following the first injection (four, 12 and 24 weeks following AS). The researcher will document adverse events and blood will be drawn to assess safety laboratory markers (FBS, ALT, AST, ALP and GGT). The diameter of the treated cyst will be captured and cyst volume will be calculated. The primary endpoint of this study, mean proportional change (%) in cyst diameter at four weeks after AS, will be obtained during the first follow-up visit. Furthermore, abdominal symptoms and health-related quality of life will be measured using the GIS-, PLD- and SF-36 questionnaires.

### Study withdrawal

Subjects can withdraw informed consent and leave the study at any time. The investigator will withdraw a subject from the study for any of the following reasons: pregnancy, consistent failure to adhere to protocol requirements, unacceptable toxicity of study medication, surgical interventions during the study or any other reason if in the best interest of the patient. All data generated up to the time of discontinuation from the study will be analyzed and the reason(s) for discontinuation will be recorded.

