### Sample size considerations

Recent data showed that patients treated by AS have a mean diameter reduction of 29.7 ± 19.76% after four weeks [23]. By adding pasireotide, we want to establish a decrease in cyst diameter of 50% after four weeks. A sample size of 15 patients per arm, leading to a total of 30 patients, is required to be able to obtain a significant difference between the two groups (power: 80%; α: 0.05). Taking into account the possibility of 10% protocol violators and/or dropouts, we aim to include 17 subjects per arm, giving a total of 34 patients.

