### Statistical analysis

Intention-to-treat (ITT) analyses will be used for all clinical outcome variables. The ITT sample includes all patients who received at least one dose of study medication. In addition, we will carry out a parallel analysis on the per-protocol treated population. This sample is defined as all patients who have received both injections, AS and all ultrasound measurements. The primary outcome of this study is the proportional (%) change in cyst diameter of the treated hepatic cyst four weeks after AS, as measured by ultrasound. The mean diameter of each orthogonal diameter measured by the blinded primary investigator will be used for analysis. Subsequently, we will calculate a mean diameter from the three mean orthogonal diameters. Proportional change will be calculated by dividing the reduction of mean cyst diameter at four weeks by mean cyst diameter at baseline, multiplied by 100. Depending on distribution, values will be presented as mean ± SD or as median ± interquartile range. Consequently, differences between the treatment and placebo arm will be calculated using the independent student’s t-test or the Mann-Whitney U test, respectively. Absolute reduction and volume reduction will be presented and analyzed similar to data for the primary endpoint. Cyst recurrence will be compared between both groups using Fisher’s exact test. The cyst diameter measurements from the second blinded investigator will be used as a control to evaluate intra- and interobserver variability by performing a Bland-Altman analysis. Symptoms of the GIS-questionnaire will be dichotomized (0 to oneversus two to six) and compared between the treatment and placebo arm using the chi-square test. Health-related quality of life domain scores and component scores (SF-36) will be compared between both arms using the Mann-Whitney U test. Frequency tables will be compiled for (serious) adverse events classified according to the standard World Health Organization - Adverse Reaction Terminology (WHO-ART) Body System Dictionary and preferred terms. All statistical analyses will be two-sided, with a critical significance level of 5%.

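### The withdrawal rule ends study participation, not only study medication, for non-adherence, toxicity or surgery, and so loses outcomes that the declared intention-to-treat analysis needs

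*Protocol article*

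**What the plan says.** Under Study withdrawal, the investigator is to withdraw a subject from the study for pregnancy, for the patient's best interest, and for "consistent failure to adhere to protocol requirements, unacceptable toxicity of study medication, surgical interventions during the study". The rule is worded as an obligation, and what ends is participation in the study. The same section adds: "All data generated up to the time of discontinuation from the study will be analyzed". The article provides for no outcome visit after withdrawal.

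Statistical analysis declares ITT for all clinical outcomes and defines the set: "The ITT sample includes all patients who received at least one dose of study medication". The primary outcome is compared by t-test or Mann-Whitney test at one time point, and recurrence by Fisher's exact test. The primary ultrasound is taken at the first follow-up visit, week 6, which is four weeks after aspiration sclerotherapy (AS).

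Second injection (week four) treats one kind of drug toxicity differently. If stated laboratory limits are exceeded, the second injection is withheld, and nothing says that the patient leaves the study.

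**The concern.** An ITT comparison needs an outcome for each patient whatever happened after the start of treatment. The withdrawal rule stops outcome collection because of events that treatment may cause.

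- **Toxicity.** The placebo is saline, so drug toxicity is to be expected mainly in the pasireotide arm. The Pasireotide section says that the common events cluster in the first days after treatment starts, which is before the primary scan.
- **Surgery.** The Background links strong fluid re-accumulation to failed symptom relief and a need to re-intervene, and re-accumulation is what pasireotide is meant to reduce. A patient operated on for a refilled cyst is a treatment failure on the protocol's own reasoning, yet would leave before the remaining recurrence assessments.

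At stake is whether the reported difference describes everyone who started treatment or only those who stayed. The Discussion wants a benefit large enough to justify pasireotide's costs and side effects. An estimate that leaves out patients who could not tolerate the drug answers that question poorly.

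**Working it through.** **Inputs.** Sample size considerations gives the control value: "patients treated by AS have a mean diameter reduction of 29.7 ± 19.76% after four weeks". It also gives the target: "we want to establish a decrease in cyst diameter of 50% after four weeks". The planned difference is 50 − 29.7 = 20.3 points with SD 19.76, two-sided 5% level, 80% power, a 10% allowance for violators and dropouts, and 17 per arm. No withdrawal rate is given, so every number of withdrawn patients below is an assumption.

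**1. The plan's own figure.** n per arm = 2 × [19.76 × (1.960 + 0.842) / 20.3]² = 14.87, rounded up to 15. With the allowance, 15 / 0.9 = 16.7, rounded up to 17, or 34 in total. The stated size reproduces, and this point does not depend on it.

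**2. What withdrawal removes.**

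| Withdrawn | Kept | Lost |
|---|---|---|
| Before the week 4 visit | Baseline scan | All diameters after AS, including the primary |
| After week 4, before week 6 | Baseline and 2-week diameters | Primary outcome and all later ones |
| After week 6, before week 14 | Primary outcome | 12- and 24-week outcomes, including recurrence |
| After week 14, before week 26 | Primary and 12-week outcomes | 24-week outcomes, including recurrence |

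**3. Illustrative size for the primary outcome.** Suppose k of 17 pasireotide patients leave before week 6, those who stay average 50%, the leavers would have averaged m, and controls average 29.7% with none lost.

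- Reported difference: 50 − 29.7 = 20.3.
- Difference in all patients: [(17 − k) × 50 + k × m] / 17 − 29.7.
- Overstatement: (k / 17) × (50 − m).

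With k = 2 and m = 29.7, the arm mean is (750 + 59.4) / 17 = 47.6, so the all-patient difference is 17.9 and the overstatement is 2.4 points. With m = 29.7 and k = 1, 2, 3 or 4, the all-patient difference is 19.1, 17.9, 16.7 or 15.5. If m = 50 there is no bias, and if m exceeds 50 the sign reverses.

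**4. Lost numbers are not the main harm.** Noncentral-t power at a true difference of 20.3 is 82.7% with 17 against 17, 80.1% with 15 against 17, and 76.8% with 13 against 17. The 10% allowance covers about two patients per arm. It restores numbers but cannot correct selective loss.

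**5. Type I error when there is no effect.** This was simulated with 100,000 trials, 17 per arm, normal outcomes with mean 29.7 and SD 19.76, a t-test, and pasireotide patients removed.

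| Removed from the pasireotide arm | At random | From the lowest 8 outcomes | The worst outcomes |
|---|---|---|---|
| 2 | 4.9% | 5.6% | 10.3% |
| 4 | 4.8% | 9.3% | 20.6% |

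Harm needs withdrawal that is related to outcome. Random loss does nothing to the error rate.

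**The case against.** The other side has several good points, and they limit how far the finding goes.

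- **Stopping the drug is already partly separated from leaving.** The laboratory limits cancel only the second injection. The per-protocol set needs both injections while the ITT set needs one dose, so one-dose patients were evidently expected to remain. A reader might infer that anyone stopped after the first injection has no week 6 scan; the documents do not support that. This stands. What remains is exit for other toxicity that is judged unacceptable, for non-adherence and for surgery. The Pasireotide section also describes the usual events as gastrointestinal, with mild diarrhea among them, and as easing with time.
- **Earlier data are kept, and a missing-data method may sit in an analysis plan not shown.** True, and the absence of such a method is not the point. No method recovers scans that were never taken, and any imputation would rest on untestable assumptions with 17 per arm.
- **Late exits spare the primary outcome.** This stands. A reader might infer that the primary comparison is confined to patients who needed no re-intervention. That would require surgery within four weeks of AS, for which no rate is given, and the rule does not limit surgery to the treated cyst.
- **Larger figures are tempting.** Scoring two withdrawn patients at 0% because they never have AS would give an all-patient difference of 750 / 17 − 29.7 = 14.4, an overstatement of 5.9 points, or about 40%. But the outcome is defined four weeks after AS, so such patients have no endpoint even with full follow-up, and nothing says that toxicity cancels AS. Similarly, a recurrence count of 3/15 (20%) instead of 5/17 (29%) rests on invented inputs and assumes that neither operated patient had met the recurrence criterion at an earlier visit.
- **Dosing by unblinded staff.** The ITT set is conditional on a first dose, and "The injections will be administered by an independent unblinded health professional". A reader might infer selection at that step. The same section says that this person has no part in design, execution or analysis, and no route from allocation to non-dosing is shown, so the point is minor.
- **Scans after surgery measure the surgery.** This is correct, and simply continuing the diameter analysis would be a mistake. The fix has to deal with it.

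**Conclusion.** The point holds in limited form and should be fixed. Followed as written, the withdrawal rule creates missing primary and later outcomes for reasons that may depend on arm and outcome, and this conflicts with the declared ITT analysis. It also sits uneasily with the week-four rule, which stops an injection without stating that participation ends.

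Neither size nor direction can be derived, because the documents give no withdrawal rate and no outcomes for patients who leave. The illustration of 20.3 points reported against 17.9 in all patients assumes two early exits in the pasireotide arm, none in the control arm, and leavers who would have done only as well as AS alone. One injection is a one-month depot, so leavers might have kept some drug benefit and the gap could be smaller. A reader might infer a proven bias in favour of pasireotide, but the documents support only the possibility. Loss of operated failures would flatter whichever arm has more of them.

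**What to change.** 1. Reconcile Study withdrawal, Second injection (week four) and Statistical analysis by separating the end of study medication from the end of study participation.
2. Keep the scheduled ultrasounds, above all at week 6, and the questionnaires for all randomised patients after medication stops or after non-adherence, unless the patient withdraws consent.
3. Continue follow-up after surgery too. Prespecify that re-intervention on the treated cyst counts as failure in the recurrence comparison, and that diameters measured after such surgery are not taken as treatment response.

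**Cost.** A few visits that are already in the schedule, no extra patients, and possibly a smaller effect estimate. Item 3 alters how recurrence is counted, so it must be settled before unblinding. The criteria for stopping study medication are a clinical matter and are untouched. Trial status reports the study as ongoing, and scans not taken are lost for good, so the change is useful only while follow-up is still running.
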